Despite having the same diagnosis, large inter-individual variability with regard to sensorimotor upper limb function and therapy response after motor therapy is seen in children and adolescents with uCP [43–48]. This variability has led researchers to investigate potential predictors of therapy response in order to determine which children and adolescents may benefit most from which type of upper limb therapy. Previous studies have already investigated potential neurological and behavioral predictors, however, sample sizes were often limited and only motor-based interventions were considered [32, 45, 46, 49–51]. Which predictors can be identified for somatosensory discrimination therapy remains to be investigated.

In summary, somatosensory function has shown to be crucial for upper limb motor function [1]. However, evidence underpinning the effectiveness of therapy approaches that specifically target somatosensory impairments is still scarce. Based on an earlier study, Sense for Kids has been proposed as a feasible and potentially effective therapy approach to improve bimanual performance and somatosensory function in children and adolescents with uCP. Yet, the effectiveness of this therapy to improve sensorimotor upper limb function when compared to upper limb motor therapy, its long-term effects, and potential predictors of therapy response still remain to be explored in an RCT.

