## Objectives {7}

Therefore, this study protocol describes the design of an RCT comparing the efficacy of Sense for Kids therapy and dose-matched motor therapy to improve sensorimotor upper limb function in children and adolescents with uCP, who present with tactile impairments in the more impaired upper limb. The primary objective is to investigate if somatosensory discrimination therapy results in better bimanual performance at 6 months follow-up, compared to upper limb motor therapy. Secondly, we will investigate if somatosensory discrimination therapy is superior to improve somatosensory impairments. Lastly, we will explore the potential role of behavioral and neurological predictors of therapy response. The results of this study may aid in the selection of the most effective therapy intervention, specifically for children and adolescents with uCP who present with tactile impairments in the upper limb.

We hypothesize that somatosensory discrimination therapy will result in equal improvements in bimanual performance compared to upper limb motor therapy, immediately after the intervention period. However, we expect further improvements in bimanual performance during the follow-up period for participants who received somatosensory discrimination therapy because of the improved upper limb use in daily life, but not after upper limb motor therapy. We further hypothesize larger improvements in proprioceptive function and tactile perception, both immediately after the intervention and at follow-up, in participants who received somatosensory discrimination therapy. By considering the content and organization of the somatosensory discrimination therapy, we expect a higher therapy response for children and adolescents with worse somatosensory function and better attentional functioning at baseline. Lastly, we hypothesize that the occurrence of thalamic lesions is an important predictor of therapy response, because of the crucial role this brain structure has in the processing of somatosensory information that is transmitted from the periphery to the cortex [52].

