## Statistical methods

### Statistical methods for primary and secondary outcomes {20a}

All observations will be summarized as mean and standard deviation or median and interquartile range, according to the nature of the data. Baseline comparability between groups will be visually checked based on descriptive statistics. As the participants will be randomized to the intervention or control group, statistical testing of baseline differences will not be performed [108]. To study the time effects of the intervention and to allow for comparison between both groups, linear or generalized mixed models will be applied for the primary and secondary outcome measures. By using random effects, such models correct for the relation among repeated observations within subjects. An additional benefit of these models is that they provide a valid inference for missing values that are (completely) at random [109]. In case the data of an outcome measure is not normally distributed based on the Shapiro–Wilk test and/or visual inspection of the data distribution, transformations will be applied. The main endpoint will be to investigate if there is a difference in evolution of the AHA score over time between both groups. As such, interactions between therapy and time will be analyzed to test for differences in improvements over time between both groups (time*group interaction effect). When a significant interaction is identified, time trends will be tested in both therapy groups separately (time-effect). When the interaction is not significant, the main effect of time will be explored. Effect sizes for the full models will be further calculated using the Cohen’s partial η^2^ formula [partial η^2^ = (F × df_between_)/((F × df_between_) + df_within_)] [110]. Significant time trends will be further investigated with pairwise post hoc tests to compare individual time points (*T*_0_–*T*_1_, *T*_1_–*T*_2_, *T*_0_–*T*_2_). For the model of the primary outcome measure, the post hoc analysis will be Bonferroni corrected and the pairwise post hoc test for *T*_0_–*T*_2_ will be the primary outcome. For the models of secondary outcome measures, a false discovery rate with an adjusted *p*-value of 0.05 will be implemented. Effect sizes of these comparisons will be calculated using Cohen’s d formula [111]. For the second research objective, we will investigate predictive factors of therapy response. Both behavioral and neurological characteristics, i.e., somatosensory function at baseline, attentional functioning, and thalamic volume, will be included as covariates in the model for the primary outcome measure. All statistical analyses will be performed in SPSS Statistics for Windows. Level of significance will be set at 0.05, two-sided. When needed, adapted statistical techniques will be applied in close collaboration with Leuven Biostatistics and statistical Bioinformatics Centre (L-BioStat).

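### As written, the predictors of therapy response enter the AHA model only as covariates, which tests association with average AHA level and not with change or with differential change by therapy

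*Protocol article*

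**What the plan says.** Statistical methods {20a} states that "linear or generalized mixed models will be applied for the primary and secondary outcome measures", with random effects to handle repeated observations within a child. The interaction it names is the one for the main endpoint: "interactions between therapy and time will be analyzed to test for differences in improvements over time between both groups (time*group interaction effect".

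The predictor aim follows later in the same section: "For the second research objective, we will investigate predictive factors of therapy response". The method given is that "somatosensory function at baseline, attentional functioning, and thalamic volume, will be included as covariates in the model for the primary outcome measure". No predictor-by-time or predictor-by-group-by-time term appears there, and the section on additional analyses {20b} only refers back to {20a}.

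Objectives {7} presents the predictor aim as exploratory. Reasoning from the content of the somatosensory therapy, it states that "we expect a higher therapy response for children and adolescents with worse somatosensory function and better attentional functioning at baseline", and also that "we hypothesize that the occurrence of thalamic lesions is an important predictor of therapy response". The Discussion adds that the predictor results may help to individualise upper limb therapy.

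Table 1 gives the primary metric as change, with T0 and T2 as the timepoints of interest.

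**The concern.** Response to therapy is a change in AHA. A hypothesis about who responds to somatosensory therapy also raises the question whether that relation differs from the one under motor therapy. A baseline characteristic added to a repeated-measures model without interactions addresses neither. It shows whether children with that characteristic have higher or lower AHA scores overall.

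The risk of a misleading result is realistic. The Background reports that somatosensory impairment goes with worse motor performance and less use of the impaired limb in bimanual activities, so baseline somatosensory function is likely to track AHA level whether or not it predicts response. Such a marker could be published as a predictor of response, while a characteristic that truly separates responders from non-responders could go unseen. The sample was enlarged from 21 to 25 per group partly for prediction, so this analysis carries some weight in the design.

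A second, smaller mismatch is that the thalamic hypothesis concerns whether a lesion is present, whereas the analysis uses volume. These are different variables.

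**Working it through.** **Inputs from the protocol (Sample size {14}).** SD of AHA improvement 5.5; planned between-group difference 5; two-sided alpha 0.05; 21 per group needed, 25 per group recruited. The protocol gives no figure for the predictor analysis. Its own calculation reproduces: 5/5.5 = 0.909 (stated as 0.9), and a two-sided two-sample t test with 21 per group at 0.9 has power 0.81.

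**Assumptions, not in the protocol.** Between-child AHA SD 15; correlation of predictor with AHA level 0.3 or 0.5; slopes as stated below; complete data at three visits; T1 change half of T2 change.

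**Step 1: what the covariate tests.** For child i at visit t:

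AHA(i,t) = visit effect + group effect + (visit × group) effect + γ·x(i) + u(i) + e(i,t)

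Subtracting T0 from T2 cancels both γ·x(i) and u(i). Expected change therefore does not depend on x, whatever γ is. This is algebra and needs none of the assumptions.

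One simulated dataset (25 per arm, true between-arm slope difference 5 per SD) shows it. The T2 time-by-group estimate was 4.352 (SE 1.543) without the covariate and 4.352 (SE 1.543) with it. The three-way model recovered the modifier: 4.802 (SE 1.319).

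**Step 2: a predictor of level that is unrelated to response.** Per-visit error variance is 5.5²/2 = 15.1, or 15.1/3 = 5.04 for a three-visit mean. The correlation of the predictor with that mean is r × 15/√(225 + 5.04) = r × 0.989, so 0.297 for r = 0.3 and 0.494 for r = 0.5. Share of 4,000 simulated trials with a significant covariate:

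| r | 42 children | 50 children |
|---|---|---|
| 0.3 | 48–49% | 55% |
| 0.5 | 92% | 96% |

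The predictor-by-time and three-way tests stay near 5%. A between-child SD from 10 to 20 moves the r = 0.5 correlation only from 0.488 to 0.497, and the rates by about two percentage points at most.

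**Step 3: real predictors.**
- Modifier only, between-arm slope difference 5 AHA units per SD: covariate term significant in 5%; three-way term in 76–77% (42 children) and 84% (50).
- Predictor of change in both arms, 3 units per SD, unrelated to baseline level: covariate term about 10%; predictor by time 90% and 94–95%.

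**Step 4: what the interaction terms could detect.** For a continuous predictor per SD, the standard error of the slope difference in T0–T2 change is 5.5 × √(2/n):

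| n per arm | SE | power, 5 units | power, 2.5 units | difference detectable at 80% power |
|---|---|---|---|---|
| 21 | 1.70 | 0.82 | 0.30 | 4.9 |
| 25 | 1.56 | 0.88 | 0.35 | 4.5 |

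Step 3's simulated power is a little lower because the predictor's sample SD also varies. For a yes/no predictor such as lesion occurrence, with an assumed prevalence of 50% to 30%, power for a 5-unit difference in treatment effect is 0.35 to 0.30 with 25 per arm.

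**Step 5: the change-score reading.** If the outcome were T0–T2 change, as Table 1 could suggest, a covariate would test association with change averaged over both arms. That covers response in general, but not whether it differs by therapy.

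**The case against.** The strongest defence is that one condensed sentence is being read as a full specification. The term covariate does not exclude interactions, the article leaves room for modified methods in consultation with the biostatistics centre, and the exact terms of an exploratory model often sit elsewhere. This lowers certainty about what will be run. It does not supply the missing terms: the same section writes out time by group where an interaction is meant, and names none for the predictors.

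Table 1's change metric is a fair point. It softens the concern about response, but the difference between therapies would still be untested, and {20a} describes repeated observations.

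Several stronger readings are tempting and are not supported:
- The Background phrase "which children and adolescents may benefit most from which type of upper limb therapy" might be taken as this trial's objective. It describes why earlier researchers studied predictors. The case for a between-therapy contrast rests on the hypothesis in Objectives {7} and on the Discussion.
- A reader might infer that children without a usable scan would drop out of the primary analysis. The covariates are introduced in a separate sentence for a separate objective, and nothing places them in the primary test.
- A reader might treat the lack of a described method for thalamic volume as an error, or prescribe a thalamic score from the semi-quantitative MRI scale. The first is detail that an article may omit; the second is not named in the documents, which mention only global and regional subscores.

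**Conclusion.** The concern holds in limited form. As written, the analysis of predictors does not match its aim: the covariate term tests average AHA level or, on the change-score reading, change pooled over arms. The level-versus-change result is algebraic. The error rates are illustrations that depend mainly on the assumed correlation of 0.3 to 0.5 between predictor and AHA level, and little on the assumed SD of 15.

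A reader might conclude that the objective cannot be answered. That goes too far, because the planned data are sufficient once the terms are named. Nor should the corrected analysis be oversold: power of about 76% to 88% for the three-way term assumes a slope difference per SD as large as the whole effect for which the trial is powered, and at half that size it is about 30% to 35%. The aim is exploratory, and the primary comparison is unaffected.

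The mismatch between lesion occurrence and thalamic volume stands as an inconsistency between Objectives {7} and {20a}.

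**What to change.** In {20a}, replace the covariate sentence with separate exploratory models, one per predictor and apart from the primary analysis:

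1. Test predictor by time, without the three-way term or averaged over arms, as prediction of response.
2. Test predictor by group by time, with its lower-order terms, as differential response to the two therapies.
3. Report the T0–T2 contrast for each with a 95% confidence interval, and state that precision is limited at 50 children, citing the power figures above.
4. Name one thalamic variable obtainable from the planned MRI, either lesion occurrence or volume, and use it in both the hypothesis and the analysis.

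The cost is a change of wording, a few more models and wide intervals. No new data are needed.

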Somatosensation comprises all aspects of touch and proprioception that contribute to a person’s awareness of his or her body parts in space and the direct interface of these body parts with objects and the environment in the absence of vision [13]. Somatosensory impairments can occur across different modalities of somatosensation, including tactile registration, tactile perception, and proprioception. Tactile registration comprises the awareness of an external stimulus, while tactile perception also includes its interpretation [14]. Proprioception, on the other hand, refers to the ability to perceive limb positions and movements [15]. For example when filling a drinking cup, tactile registration and perception are needed to provide information on the cup’s texture and weight which is needed to adequately tune grip force [16], while proprioception ensures that the position of both hands relative to each other is properly maintained as the cup is filled and its weight increases [17].

As such, accurate somatosensory information is crucial for motor control and motor learning [1, 18, 19]. In children and adolescents with uCP, the presence of somatosensory impairments has shown to be related to worse motor performance, diminished fine motor skills, and reduced use of the impaired upper limb during bimanual activities [10, 20–25]. As a result, developmental experiences will be restricted, limiting somatosensory input and motor development even more [6]. This vicious circle emphasizes the importance of addressing these somatosensory impairments during rehabilitation [26, 27], to improve the use of the more impaired upper limb during bimanual daily life activities potentially further and as such stimulate developmental experiences, functional independence, and quality of life.

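### Predictors of therapy response enter the repeated-measures AHA model as covariates with no stated interaction, which tests their relation to AHA level rather than to change or differential response

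*Protocol article*

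**What the plan says.** All of the following is in the protocol article.

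- **Model.** Statistical methods {20a} plans linear or generalized mixed models on the repeated scores, and notes that "such models correct for the relation among repeated observations within subjects". The comparison of therapies is carried by an interaction: "interactions between therapy and time will be analyzed to test for differences in improvements over time between both groups".
- **Predictors.** The same section announces that "we will investigate predictive factors of therapy response". It lists "somatosensory function at baseline, attentional functioning, and thalamic volume", and says these "will be included as covariates in the model for the primary outcome measure". It names no interaction of a predictor with time or with group. The item on additional analyses {20b} only refers back to {20a}.
- **Question.** Background {6a} asks "which children and adolescents may benefit most from which type of upper limb therapy". Objectives {7} reasons from the content of the somatosensory therapy: "we expect a higher therapy response for children and adolescents with worse somatosensory function and better attentional functioning at baseline". Table 1 gives change between T0 and T2 as the metric of the primary outcome.
- **Relation to level.** Background {6a} also reports that "the presence of somatosensory impairments has shown to be related to worse motor performance", and that the impaired limb is used less in bimanual activities.

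**The concern.** Each predictor is a single baseline value per child. In a model for AHA at three visits, the coefficient of such a covariate is the difference in AHA averaged over the visits per unit of the covariate. Response is the difference between visits, and the averaging removes it as a separate quantity. Differential response would need a further interaction with group.

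Two errors follow. A variable that only marks severity can be reported as a predictor of response. A variable that does predict change but is unrelated to level will usually be missed. For somatosensory function, the document's own premises even point in opposite directions: worse function is expected to go with a lower AHA level but with a larger gain. A significant covariate could then carry the wrong sign for response.

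The sample was raised to 25 per group partly for prediction purposes, and the Discussion hopes that the results may help to individualise therapy.

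**Working it through.** **Inputs from the protocol.** SD of AHA change 5.5; 25 per group; two-sided alpha 0.05; visits T0, T1, T2. The sample size reproduces: an exact two-sided t-test at effect size 0.9 needs 21 per group (power 0.81). That figure is not in dispute.

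**Assumptions, not in the protocol.** SD of AHA level at baseline 15 (10 to 20 tried); complete data; correlation 0.6 between the T0–T1 and T0–T2 changes; correlations between predictor and level or change as given below.

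**What the covariate term tests.** Let B be the baseline score and C1, C2 the changes to T1 and T2. With balanced data, the covariate main effect is tested on the child's mean M = B + (C1 + C2)/3. Predictor-by-time at T0–T2 is tested on C2.

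Var(M) = 15² + 2 × 5.5² × (1 + 0.6)/9 = 225 + 10.76 = 235.8, so the SD of M is 15.35.

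**Case 1: predictor related to level only (correlation r).** Its correlation with M is r × 15/15.35 = 0.977r. The noncentrality is ρ√50/√(1 − ρ²), with ρ = 0.977r and 47 degrees of freedom. For r = 0.3, ρ = 0.293 and the noncentrality is 0.293 × 7.07/0.956 = 2.17, which gives about 56%.

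| r with level | Covariate significant, formula | Covariate significant, simulation | Predictor-by-time |
|---|---|---|---|
| 0.1 | 10% | about 12% | about 5% |
| 0.2 | 28% | about 28% | about 5% |
| 0.3 | 56% | about 55% | about 5% |
| 0.5 | 97% | about 96% | about 5% |

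Over 42 to 50 children and level SD 10 to 20, the simulated rates are 46–56% at r = 0.3 and 89–96% at r = 0.5.

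**Case 2: predictor related to change only (r = 0.5 with C2, both arms).** The predictor's slope on C2 is 0.5 × 5.5 = 2.75 units per SD. If 0.6 of that is present at T1, its slope on M is 2.75 × 1.6/3 = 1.47. Its correlation with M is then 1.47/15.35 = 0.096, and detection is about 10%. Simulated detection with 50 children is 16%, 10% and 9% at level SD 10, 15 and 20. It reaches about 30% at level SD 10 if the whole effect is present at T1 and a shift of 3.2 units per SD is added to a residual SD of 5.5 (total SD √(5.5² + 3.2²) = 6.4). Predictor-by-time detects the effect in about 96% of trials.

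**Case 3: predictor of change in the somatosensory arm only (r = 0.5 there, 0 in the other arm).** The covariate is significant in 5–8% of trials. The three-way term is significant in 36–43%, and in 48% in the setting with the larger shift.

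**Case 4: opposite signs.** Suppose better function has r = 0.5 with level and r = −0.5 with change in the somatosensory arm. With level SD 15, the slope on level is +7.5 units per SD, and the slope on T0–T2 change in that arm is −2.75. The slope on M in that arm is 7.5 − 1.47 = +6.03; in the motor arm it is +7.5; the average is +6.77. The covariate is significant in 81–93% of trials, and its sign is opposite to that of the response.

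**Check with a fitted mixed model** (50 children, level SD 15, 150 trials per case, r = 0.5). A level-only predictor was significant in 97% as a covariate and 4% with time. A change-only predictor was significant in 11% and 95%. Adding the covariate left the time-by-group estimate unchanged to rounding.

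**The case against.** **The wording is short and not exclusive.** The section does not say that predictors enter as main effects only. It sits in a condensed article, it allows adapted techniques in consultation with a biostatistics centre, and it treats change as the quantity of interest elsewhere. A well-disposed analyst might add the interactions. This stands in part: the protocol does not rule them out. But it states how the predictors enter, spells out the interaction for group, and gives none for the predictors. If the outcome were read as a change score, a plain covariate would test change pooled over both arms, which still does not show who benefits from which therapy.

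**False predictors are not certain, and not equally likely for all three.** This stands. The protocol links only somatosensory impairment to motor performance; nothing links attention or thalamic volume to AHA level. Every participant must have a tactile impairment, so the range is restricted and the correlation within this trial may be weak. At correlations of 0.1 to 0.2 the excess is moderate.

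**The aim is exploratory.** This also stands. The Abstract and Objectives describe it as exploration, and the Discussion says only that the results may aid individualisation.

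**A stronger reading to avoid.** A reader might infer that children without a usable MRI scan or questionnaire score drop out of the primary result. The text does not support this. It completes the primary analysis, including the T0–T2 comparison, before it turns to predictors, and it does not say that the primary result comes from the fit with covariates.

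**Conclusion.** Followed as written, the predictor analysis answers a different question from the one posed: association with average AHA level, not with change or with differential response. That mechanism follows from the model and does not depend on the assumed values.

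The size does. It rests on an assumed level SD, assumed correlations, complete data and, for predictors of change, on how much of the effect is already present at T1. The rates in the working therefore show a strong tendency and are not forecasts for each predictor. The case is clearest for somatosensory function, where the protocol itself makes a relation to level plausible.

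A reader might take this as a flaw in the primary analysis. It is not: with complete data the time-by-group estimate is the same with or without the covariates, and the sample size is untouched. The point should be fixed before analysis, but it is not critical to the trial.

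**What to change.** In Statistical methods {20a}, replace the covariate sentence with a statement along these lines:

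- Each predictor is studied in its own exploratory model for AHA, containing predictor-by-time and predictor-by-group-by-time with all lower-order terms.
- Prediction of response is read from the T0–T2 component of predictor-by-time, or from arm-specific slopes. Differential response is read from the T0–T2 component of predictor-by-group-by-time.
- Results are reported as estimates with 95% confidence intervals and labelled exploratory.
- The three-way term is imprecise at this sample size: power is about 36–49% even if the predictor correlates about 0.5 with change in one arm and not at all in the other. A non-significant result is therefore not evidence that the therapies suit the same children.

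The cost is a few sentences and a few extra models. No new data or participants are needed. Recruitment is planned to run until June 2027 at the latest, so the terms can still be fixed before analysis.
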